### **3.e Quality Assurance of Diagnostic Testing**

Before beginning enrollment, eligible sites and readers will be qualified by the Diagnostic Testing Coordinating Center (DTCC) based on site and reader surveys, on successful transfer of 1 or more complete data sets with sufficient image quality and completeness for each modality, and participation in the CTA case review. Site qualification will be issued by the DTCC for each modality before subject enrollment.

---

During the study, technical quality assessment of image and test acquisition will be accomplished on all studies by central repository research technicians trained by the DTCC or by the CCC for invasive coronary angiography. This ongoing review will ensure the adequate quality and completeness of data sets (see details and definitions in the MOP) and will monitor radiation exposure in the CTA arm throughout the trial.

Expert overreading of the initial, randomized, noninvasive tests and first invasive angiogram within 60 days of randomization will be performed in approximately 10% of subjects by modality experts in the DTCC and CCC. To ensure protocol compliance early on and to account for low-accrual sites, the first 2 studies and ~10% of the remaining studies from each site will be overread in each modality. These will be selected by block randomization stratified by testing site and test modality.

In addition, to strengthen the link between site investigator reported invasive catheterization without obstructive disease and angiographic findings, a sample of invasive angiograms determined by site investigators to be without obstructive disease will undergo core lab QCA and the results compared.

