***E5 Independent Clinical Event Adjudication Committee***

An independent clinical event adjudication committee will review and adjudicate all primary endpoint events and the catheterization secondary endpoints in a blinded fashion based on the definitions presented above. If the invasive cardiac catheterization report is inconclusive, the CEC will review the catheterization films for a visual assessment of CAD. The other clinical secondary endpoint events and cumulative radiation exposure will not be adjudicated.

Primary outcome events will be documented through 60 (+/- 14) days after randomization by the site Investigator or authorized designees. After that, the DOFG or its designees will be responsible for documenting study events from 6 months until the end of the study.

---

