The second important component of information from the diagnostic test QA activity is the quality of test interpretations. Approximately 10% of tests will be overread by the DTCC using a categorical level of coronary disease risk. The site interpretation of level of risk will be compared with the level of risk using the same scale assessed by the core lab's overread of the test, and overall summary statistics of the agreement between the site and core lab assessments will be computed. Raw proportions of agreement (perfect agreement, and agreement differing by less than or equal to 1 category of risk) will be tabulated, and Kappa statistics will be used to characterize the level of agreement. The Kappa statistics are "chance corrected" (i.e., adjusted for agreement due to chance), and both unweighted and weighted Kappa statistics will be used in these analyses since more substantial disagreements in the assessment of risk for a given subject would be more serious than small disagreements. These agreement statistics will then be compared across the different testing modalities to determine whether the level of agreement between the site readings and the core lab readings varies with the type of test.

Another important component of information to characterize data quality for the secondary endpoints that involve non-obstructive CAD will be the review of selected

---

coronary angiograms to determine the degree to which site-reported assessments of non-obstructive coronary disease are concordant with carefully-performed core lab QCA. The same type of agreement statistics as described above, including raw proportions of agreement and chance-corrected Kappa statistics, will be used to describe and characterize the accuracy of the site-reported assessments of non-obstructive CAD.

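### The core-lab QCA sample contains only angiograms the site called non-obstructive, so the planned two-category kappa is 0 or undefined and this comparison cannot detect over-called obstructive disease

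*Supplement*

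**What the plan says.** Three parts of Protocol Amendment 2 bear on this point.

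- **QCA sample (D3 3.e, last paragraph).** To support site-reported catheterizations without obstructive disease, "a sample of invasive angiograms determined by site investigators to be without obstructive disease will undergo core lab QCA and the results compared". No sample size is given.
- **QCA analysis (F2 2.c, last paragraph).** Selected angiograms will be reviewed to determine "the degree to which site-reported assessments of non-obstructive coronary disease are concordant with carefully-performed core lab QCA". The same kinds of agreement statistic as for the test overreads, "including raw proportions of agreement and chance-corrected Kappa statistics, will be used to describe and characterize the accuracy of the site-reported assessments of non-obstructive CAD". This section gives no selection rule of its own and mentions no site-called obstructive films, so D3 3.e holds the only stated rule.
- **Other checks.** D3 3.e also plans expert overreading of the initial noninvasive tests and of the "first invasive angiogram within 60 days of randomization will be performed in approximately 10% of subjects by modality experts in the DTCC and CCC". On how the overread studies are chosen it says: "These will be selected by block randomization stratified by testing site and test modality". Under E5 the events committee "will review and adjudicate all primary endpoint events and the catheterization secondary endpoints in a blinded fashion based on the definitions presented above". E5 adds: "If the invasive cardiac catheterization report is inconclusive, the CEC will review the catheterization films for a visual assessment of CAD".

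SAP section 7.2.1 repeats that the classification rests on visual assessment and blinded adjudication. The SAP contains no plan for the QCA agreement analysis, so it neither changes nor mends the protocol text.

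**The concern.** Kappa compares two raters beyond chance and needs both to vary. Here the sample is selected on one rater's answer, so the site rating is constant and kappa carries no information about the sites.

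The selection also removes one of the two possible errors from view. A film the site calls non-obstructive and QCA calls obstructive can be seen. A film the site calls obstructive and QCA calls non-obstructive cannot, because it is never sampled. That second error is the one that could leave events out of secondary endpoints #1 and #5.

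Catheterization without obstructive CAD is the only component that separates secondary endpoint #1 from the primary endpoint (SAP 7.2.1). SAP section 18 names #1 the key secondary endpoint and places it directly after the primary in interpreting the trial. Noninvasive test results go to the care team (D3 3.b), so the angiogram may be read with the initial result known. Error rates that differ by arm are plausible, though nothing in the documents shows that they occur.

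**Working it through.** The plan states no kappa, sample size or precision for this comparison, so there is no figure to reproduce. The check is algebraic.

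**Inputs.** The site call is non-obstructive for every sampled film (D3 3.e). The statistics are raw agreement and kappa (F2 2.c). Let p be the share of these films that QCA confirms as non-obstructive.

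**Sample as written.** Kappa = (Po − Pe)/(1 − Pe).

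- Site margins: 1 non-obstructive, 0 obstructive. QCA margins: p and 1 − p.
- Po = p.
- Pe = 1 × p + 0 × (1 − p) = p.
- Kappa = (p − p)/(1 − p) = 0 for p < 1, and 0/0 for p = 1.

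Illustration with an assumed 200 films:

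| QCA confirms | Po | Pe | Kappa |
|---|---|---|---|
| 100% | 1.00 | 1.00 | undefined |
| 99% | 0.99 | 0.99 | 0 |
| 95% | 0.95 | 0.95 | 0 |
| 90% | 0.90 | 0.90 | 0 |
| 80% | 0.80 | 0.80 | 0 |
| 70% | 0.70 | 0.70 | 0 |
| 50% | 0.50 | 0.50 | 0 |

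Weighting does not help while the site rating is constant: the joint table then equals the product of its margins, so observed and chance-expected disagreement coincide under any weights. Raw agreement remains interpretable, but only as p.

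**What the sample cannot see.** Assume 40% of first catheterizations are site-called non-obstructive and QCA confirms 90% of those. Compare two cases for the obstructive calls.

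- QCA confirms 90%: the over-called share of all catheterizations is 0.60 × 0.10 = 6%. With both calls sampled, Po = 0.36 + 0.54 = 0.90, Pe = 0.40 × 0.42 + 0.60 × 0.58 = 0.516, and kappa = 0.384/0.484 = 0.79.
- QCA confirms 70%: the over-called share is 0.60 × 0.30 = 18%. Po = 0.36 + 0.42 = 0.78, Pe = 0.40 × 0.54 + 0.60 × 0.46 = 0.492, and kappa = 0.288/0.508 = 0.57.

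The planned sample returns the same result in both cases: confirmation 0.90, kappa 0.

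**Range after sampling both calls.** The site-called non-obstructive share was set at 40%, 50% and 60%. Five pairs of confirmation rates (non-obstructive/obstructive) were tried: 95/95, 90/90, 95/80, 90/70 and 80/80%. Kappa runs from 0.57 to 0.90. None of these rates is in the documents.

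**Why sampling fractions matter.** Take 132 non-obstructive and 48 obstructive films, each 90% confirmed, from a population that is 40% site-called non-obstructive. Unweighted, Po = 0.90, Pe = 0.587 and kappa = 0.313/0.413 = 0.76. Weighted back to the population, it is the 0.79 above.

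**The case against.** The best defence is that the QCA sample does what its stated purpose requires. It verifies the site calls that create endpoint events, and raw agreement, which is already planned, is exactly the confirmation rate. A reader who sees a high raw agreement beside a kappa of 0 might not be misled. The comparison feeds no test and reclassifies no patient, and the endpoint is defined by visual assessment, not QCA. All of that stands and limits the consequence. It does not rescue kappa, and F2 2.c sets the aim as accuracy of the site assessments, which also needs the obstructive calls.

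Three stronger readings are tempting, and the documents do not support them.

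- **Over-called obstructive disease goes wholly unchecked.** The approximately 10% overread of first angiograms is not selected by the site's call, so site-called obstructive films are eligible. The check is limited: it is not QCA, F2 2.c does not link it to the non-obstructive CAD agreement analysis, and it covers the first 60 days while the SAP endpoint runs to 90.
- **QCA is the only independent check.** A blinded committee adjudicates the catheterization endpoints, so a site call does not by itself settle an event. The limit is that film review is specified only for an inconclusive report; a confident but wrong report would not trigger it under E5.
- **Kappa is always exactly zero.** It is undefined if QCA confirms every film. If sites graded stenosis within the non-obstructive films, kappa could differ from zero. F2 2.c borrows statistics that include weighted kappa, but describes no graded scale for the QCA comparison.

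**Conclusion.** Wrong as written, with moderate consequence. On the QCA sample D3 3.e defines, the two-category kappa planned in F2 2.c is 0, or undefined at full confirmation, whatever the sites' accuracy. The same comparison cannot detect obstructive disease over-called by sites.

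This rests on two assumptions: that the comparison is the binary obstructive/non-obstructive call, and that D3 3.e is the complete selection rule. The documents state nothing to the contrary on either.

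The effect is on the data-quality support for secondary endpoints #1 and #5. The primary endpoint and its test are untouched. The documents do not allow the size of any misclassification, or any difference between arms, to be estimated.

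**What to change.** Draw the same number of QCA reads from first catheterizations in the endpoint window, taking films with each site call at known sampling fractions, with readers blinded to site call and randomized arm. Report the QCA confirmation proportion for each call with a CI, and kappa weighted by the inverse sampling fractions. State the window in the sampling rule, since Amendment 2 uses 60 days and the SAP uses 90.

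The cost is a different sampling list rather than more reads. The downside is fewer non-obstructive films and less precision per cell, so comparisons between arms should be labelled descriptive.

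If only the one-sided sample exists, delete kappa, report the confirmation proportion with a CI overall and by arm, and state that the sample says nothing about obstructive calls. This needs no new reads.

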### ***Feedback to Clinical Sites, Remediation, and Disqualification***

Sites whose performance does not consistently meet the quality criteria for both quality assurance (QA) and radiation exposure will be asked to undergo protocol review and retraining up until March 31, 2013. Sites that fail to improve may be recommended for discontinuation of enrollment.

### **3.f Subsequent Medical Care**

Care following the imaging studies will be provided by the local care physicians at their discretion. However, they will be encouraged to follow established guidelines for the management of CAD or for primary prevention. To this end, test-information sheets specific to each modality will be created and supplied to each enrolling site and physician and to relevant imaging site staff. These will consist of a brief literature review of diagnostic and prognostic indications of various test results.

In addition, primary and secondary prevention information sheets will be created and provided to each enrolling site and physician at the beginning of the trial. These will consist of brief summaries of relevant ACC/AHA Guidelines and will be referenced to the test-information sheets' results.

### **3.g Testing Risk and Benefits**

To be eligible for entry into the study, each subject and his or her health care provider will have considered the risks and benefits of noninvasive testing and will have determined that the incremental information gained outweighs the potential risks. For example, although diagnostic testing provides important diagnostic and prognostic information and is noninvasive, it cannot be used indiscriminately. Associated risks include maximal exercise testing, use of pharmacologic stress and contrast agents, and radiation exposure on the order of 7 to 17 mSv for stress nuclear and CTA (although aggressive dose-reduction strategies can reduce this to ~2–6 mSv in CTA). Computed tomographic angiography also often involves the use of beta blockers to lower heart rate and an angiographic contrast agent. (For comparison, the radiation exposure from a single-view chest x-ray is about 0.03 mSv).

---

Because the long-term risks and benefits of one form of testing vs. another are unknown, the PROMISE trial is collecting all relevant information to address these knowledge deficiencies, including test complications and estimated total biological radiation exposure for cardiovascular procedures during the duration of the trial. For radiation, doses will be estimated whenever possible using the site's specific scanning protocols for diagnostic testing and fluoroscopic time for invasive procedures. However, if these are unavailable or deemed unreliable, modeled estimates from the sites with such data or from the relevant literature will be used. We will also record the presence of incidental findings as reported on all initial tests and follow-up procedures (including surgical procedures) or testing performed to further evaluate any resulting new diagnoses of significant noncardiac disease.

## **E Study Procedures**

### **E1 *Screening for Eligibility***

Screening of subjects for this trial will be conducted by the site investigator (or authorized designees) at each participating site. Written, informed-consent documentation will be obtained from each prospective trial subject once study eligibility is confirmed and before the first study procedure.

### **E2 *Schedule of Assessments***

Subjects will be screened and randomized at or before time of enrollment. Baseline medical history, blood work, and QOL will be assessed. Subsequently, subjects will have either a telephone call or clinic visit at 60 (+/- 14) days for outcome evaluation and recording of any test complications. After that, subjects will be contacted under DOFG supervision by either DOFG or its trained designees at 6 months postrandomization and at 6-month intervals for subsequent follow-up assessments until death, withdrawal, or the end of the trial.

Screening assessments are described below.

| TABLE OF ASSESSMENTS                  | Screening/
Day 1 | Day
1-30 | Day
60  | 6
mos       | 12
mos      | 18
mos      | 24
mos      | 30
mos      | 36
mos      |
|---------------------------------------|---------------------|-------------|------------------------|----------------|----------------|----------------|----------------|----------------|----------------|
| Informed Consent                      | X                   |             |                        |                |                |                |                |                |                |
| Confidential Patient Information Form | X                   |             |                        |                |                |                |                |                |                |
| Medical History                       | X                   |             | X          | X  | X  | X  | X  | X  | X  |
| Concomitant Medications               | X                   |             | X                      | X              | X              | X              | X              | X              | X              |
| CV Risk                               | X                   |             |                        | X              | X              | X              | X              | X              | X              |
| Pregnancy Test            | X                   |             |                        |                |                |                |                |                |                |
| Creatinine                | X                   |             |                        |                |                |                |                |                |                |
| Resting 12-lead ECG       | X                   |             |                        |                |                |                |                |                |                |
| Quality of Life           | X                   |             |                        | X              | X              |                | X              |                |                |
| Economics                             | X                   |             |                        | X              | X              | X              | X              | X              | X              |
| Biomarker Banking                     | X                   |             |                        |                |                |                |                |                |                |
| Randomization                         | X                   |             |                        |                |                |                |                |                |                |
| Initial Diagnostic Test               |                     | X           |                        |                |                |                |                |                |                |
| Clinical Assessment                   |                     |             | X                      | X              | X              | X              | X              | X              | X              |
| Endpoint Assessments                  |                     |             | X                      | X              | X              | X              | X              | X              | X              |
| Test Safety Assessment                |                     |             | X                      |                |                |                |                |                |                |

mos=months; CV=cardiovascular; ECG=electrocardiogram

 +/- 14 days

 During medical history review, if subjects have received an additional diagnostic test, a cardiovascular procedure or have been hospitalized since the last visit, additional data will be collected from the practice or institution with subject consent

 Pregnancy test required only for female subjects of childbearing potential

 Creatinine blood draw required only for subjects without a recent normal value (within previous 90 days)

 Resting 12-lead ECG required if none available within past 30 days

 Quality of Life assessments will be performed in ~ 6000 subjects enrolled (prior to July 2012).

### Day 0/1 Screening/Randomization:

- The subject's relevant medical history (including concomitant medications) will be obtained.
- Coronary arterial disease risk factors will be assessed, including BP/hypertension, PAD (ratio of arm to leg systolic BPs or formal ABI), cerebrovascular disease (carotid bruits), diabetes, cholesterol (LDL, HDL), smoking, family history, sedentary life style, obesity.
- Factors increasing probability of CAD (including diabetes, PVD, and/or other CAD risk factors) will be documented.
- Cardiac symptoms and chest pain descriptors will be assessed.
- Eligible subjects will be asked to give consent for study participation.
- If the subject is of childbearing potential, a pregnancy test will be performed.
- Creatinine blood draw will be done if there is no creatinine measurement within the previous 90 days.

- 
- Subjects will receive a 12-lead resting ECG unless one obtained within the past 30 days is available.
  - Subjects will be administered baseline QOL questionnaires at the time of randomization.
  - A blood sample will be drawn on subjects participating in biomarker and/or genomic banking (See Section E8).
  - The subject will be randomized to the functional test of investigator or care provider choice or CTA. (*Note: functional test of choice must be selected and documented before placing the call to randomize the subject.*)

**Days 1-30:**

- The functional diagnostic test or CTA will be performed according to the randomized assignment.

**Day 60 (+/- 14 days) Postrandomization Follow-up Assessment—site clinic visit or telephone call:**

- Relevant interval medical history (including symptoms and concomitant medications) since last assessment will be obtained, including death, MI, major complications from cardiovascular procedure or testing (stroke, major bleeding, anaphylaxis, renal failure), unstable angina hospitalization.
- Test images and stress ECGs from the first test (and the randomized test, if different) will be uploaded to the DTCC. If applicable, the subject's first invasive coronary angiography report and images will be uploaded to the DTCC. All clinical test reports will be sent to the CCC at the DCRI.
- The results of any additional noninvasive tests or invasive catheterizations performed within the first 60 days will be collected.
- Radiation exposure will be assessed.
- Interval resource consumption, including hospitalizations, will be assessed.
- Patient satisfaction will be assessed.

**Follow-up at 6 months postrandomization and every 6 months thereafter will be conducted by DOFG staff or its trained designees:**

- Relevant interval medical history (including symptoms and concomitant medications) since last assessment will be obtained, including death, MI, major complications from study-related cardiovascular procedures (e.g. catheterization, PCI, CABG, CTA, stress echo, stress nuclear) or testing (stroke, major bleeding, anaphylaxis, renal failure), unstable angina hospitalization.
- Interval radiation exposure will be assessed.
- Interval resource consumption, including hospitalizations, will be assessed.
- Cardiovascular risk modification will be recorded.
- QOL questionnaires will be completed at 6 months, 12 months, and 24 months post-randomization (among patients followed for 24 months).

---

